## Proposed Analysis

In the first step, a cumulative frequency will be calculated for each of the enhanced privacy aspects captured in the hypothetical premium versions of Facebook (**Figure 5**).

**FIGURE 5 F5:**
[figure not shown]
Cumulative frequencies of the questions of the PSM.

In a second step, the range of acceptable prices that each participant is willing to pay for the different privacy-enhanced premium versions will be determined. The range of acceptable prices is defined by its endpoints marginal cheapness and marginal expensiveness (van Westendorp, 1976). Marginal cheapness is determined by the point where the cumulative frequencies of “too cheap” prices (reversed) and “cheap” prices intersect (MGP in **Figure 6**). In contrast, the point of marginal expensiveness is determined by the intersection of the cumulative frequencies of “too expensive” prices (reversed) and “expensive” prices (MEP in **Figure 6**).

**FIGURE 6 F6:**
[figure not shown]
Range of acceptable prices.

In a third step, we will follow the approach by Lipovetsky (2006) who proposes that the four questions of the PSM and their corresponding cumulative distributions split the price continuum into five price perception intervals. These five price perception intervals are *too cheap, bargain, acceptable price, premium*, and *too expensive*. Thus, instead of the four thresholds of the questions of the PSM (**Figure 5**), five price ranges will be considered that are defined as discrete states with a continuous price variable and modeled as ordinal logistic regressions.

Following this model, the logistic cumulative probabilities for each price threshold will be determined and the appropriate thresholds for the particular model will be subtracted (i.e., for the acceptable price model the expensive price threshold is subtracted from the cheap price threshold). This procedure leads to smooth regression lines and allows determining the maximum of a specific price perception range. These maxima will be used as a proxy for participants’ willingness-to-pay (WTP in **Figure 7**).

**FIGURE 7 F7:**
[figure not shown]
Price sensitivity for the acceptable price perception interval.

Ordinal logistic regression models will be applied to test for statistical differences between participants’ willingness-to-pay for the different privacy aspects captured in the hypothetical premium versions of Facebook. Furthermore, the regression models can be extended to multiple predictors (e.g., privacy concerns and socio-demographic characteristics), since we hypothesize that psychological characteristics influence participants’ propensity to pay for the privacy enhancements. Together with the range of acceptable prices, the proxies will be used to test for intra-individual and inter-individual differences between willingness-to-pay for the four privacy-enhanced premium versions of Facebook. In addition, repeated-measure ANOVAs will be calculated for participants’ willingness-to-pay for the four different premium versions of Facebook, using the participant answers on the overall valuation measure (i.e., *“Overall, how much would be willing to pay for this premium version of Facebook?”*) as dependent variable. Where applicable, *post hoc* tests will be employed to determine the specific group differences. Data analysis will be conducted in R studio (R Core Team, 2017) and the conventional significance level of α = 0.05 will apply to all analyses.

With respect to the theoretical model (see **Figure 4**, Section Theoretical Model), we follow previous approaches (Malhotra et al., 2004; Schreiner and Hess, 2015) and assume linear relationships between the indicated psychological variables (see Section Psychological Characteristics), which will be statistically tested using structural equation modeling to identify the path coefficients. As outcome variable in the tested model, participants’ overall willingness-to-pay for the hypothetical, full-design premium version of Facebook will be used.

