## Study Objectives and Research Hypotheses

Filling these research gaps, the overarching objectives of the present study are twofold: first, the study will explore users’ valuation of three different privacy aspects in the context of social networking services and, second, the study will investigate the psychological mechanisms underlying users’ overall valuation of privacy.

Investigating the former, three privacy aspects will be studied that are captured in Facebook’s Data Policy (Facebook Inc., 2016) as well as in Malhotra et al.’s (2004) multidimensional model of privacy. These three privacy aspects are (1) data collection, (2) data control, and (3) third party use. Accordingly, participants will be offered enhancement of these three privacy aspects within hypothetical premium versions of Facebook. Precisely, these privacy-enhanced premium versions of Facebook will offer (1) restricted data collection on side of the company, (2) enhanced data control for users, and (3) no sharing of users’ data with third parties. Willingness-to-pay for the premium versions will be used as a proxy for participants’ valuation of these privacy aspects. Expanding on previous studies (e.g., Schreiner et al., 2013), this study’s insights will provide a more detailed understanding of users’ valuation of different aspects of privacy. It is explored whether Internet users value some aspects of privacy more than others. Though previous research suggests that third-party sharing may be valued most (Esrock and Ferre, 1999; Hann et al., 2002), we argue that it is also possible that companies’ restrictions on data collection may be valued more, since if no data are collected, users may be less worried about their data being shared with third parties. At the same time, the prevailing control-centered definition of privacy may invoke stronger valuations of the data control aspect. In light of these contradictory assumptions, for the present research no directional hypotheses can be formulated for the valuation of the three privacy aspects.

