### Willingness-to-Pay Measure

Quantifying Internet users’ valuation of the different privacy aspects, the van Westendorp’s (1976) Price Sensitivity Meter model (PSM) will be employed as a willingness-to-pay measure. The PSM is a descriptive statistical procedure labeled the “psychological price” modeling (Lipovetsky et al., 2011). Rather than asking a single price indicator, the PSM allows capturing economic valuation in psychological terms. Furthermore, it ensures comparability of the results with the study by Schreiner et al. (2013). The PSM consists of four questions that ask participants to balance the value of certain products or services against the price. Precisely, participants will answer the following questions about the four premium versions (as compared to the free version) presented:

(1)At what price does this product become *too cheap*, that is, so cheap that you would question its quality and not buy it?(2)At what price does this product start to seem *cheap* to you, that is, when does it start to seem like a bargain?(3)At what price does this product start to seem *expensive* to you?(4)At what price does this product become *too expensive*, that you would not consider buying it?

The questions will be presented simultaneously and in the above order below the two versions of Facebook (i.e., conventional, free-of-charge versus hypothetical, privacy-enhanced version of Facebook). Participants will be asked to indicate a monthly price they are willing to pay for the privacy enhancement of each premium version. Combining the answers from the four PSM questions will allow identifying the upper and the lower price limit that participants are willing to pay for privacy. Based on this, the optimal price can be calculated as described in more detail in Section Proposed Analysis.

After answering the four PSM questions, a single-item willingness-to-pay measure will be employed to additionally assess the overall willingness-to-pay for the different privacy aspects (“*Overall, how much would be willing to pay for this premium version of Facebook?”)*. This overall valuation measure will be used to validate the results of the PSM and to conduct the multiple comparisons between the three privacy enhancements, which will allow drawing conclusions about which privacy aspects are valued the most.

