## Anticipated Results

In the proposed experiment, Internet users’ valuation of different privacy aspects will be investigated in the context of social networking services. Four hypothetical, privacy-enhanced premium versions of Facebook will be developed, each offering the enhancement of one specific privacy aspect, namely data collection, data control, and third party sharing. A fourth version incorporates all three privacy enhancements. Valuation of privacy will be quantified using willingness-to-pay. The main aims of the experiment are to identify differences in the valuation of the three privacy aspects as well as to unravel the psychological mechanisms underlying these valuations.

For the purpose of the study, the PSM will be employed to measure willingness-to-pay for the premium versions of Facebook. The PSM allows estimating acceptable price ranges for each of the examined privacy aspects. Ordinal logistic regression as well as ANOVAs and according *post hoc* testing will be employed to investigate within-subject valuations of the three privacy aspects (i.e., data collection, data control, and third party sharing). In a second analysis step, the proposed theoretical model encompassing relevant psychological characteristics will be tested in order to unravel the psychological mechanisms underlying valuations of privacy. We expect overall willingness-to-pay (i.e., for the full-design premium version of Facebook) to be explained by privacy concerns, mediated by the perceived risk on Facebook, as well as by several moderating variables (see Sections Theoretical Model and Psychological Characteristics).

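### Two sections of the article conflict on which test decides whether the three privacy aspects are valued differently, and every test is given the full 0.05

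*Protocol article*

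**What the plan says.** Three sections of the protocol article bear on this question.

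- **Willingness-to-Pay Measure.** The "Price Sensitivity Meter model (PSM) will be employed as a willingness-to-pay measure", and the section describes the PSM as a descriptive procedure. A single overall item follows the four PSM questions and has two roles. The first is supportive: "This overall valuation measure will be used to validate the results of the PSM". The second is deciding: the item is used "to conduct the multiple comparisons between the three privacy enhancements, which will allow drawing conclusions about which privacy aspects are valued the most".
- **Proposed Analysis.** After the PSM modelling steps: "Ordinal logistic regression models will be applied to test for statistical differences between participants’ willingness-to-pay for the different privacy aspects". Then: "In addition, repeated-measure ANOVAs will be calculated for participants’ willingness-to-pay for the four different premium versions of Facebook", with the overall item as dependent variable and post hoc tests where applicable. The section closes by stating that "the conventional significance level of α = 0.05 will apply to all analyses".
- **Anticipated Results.** Both methods are listed together for one purpose: "Ordinal logistic regression as well as ANOVAs and according *post hoc* testing will be employed to investigate within-subject valuations of the three privacy aspects". The same section calls differences between the three aspects one of the main aims.

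Under Study Objectives and Research Hypotheses the article says that "no directional hypotheses can be formulated for the valuation of the three privacy aspects".

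**The concern.** Objective 1 asks one question, and the article gives it two significance tests on two different dependent variables. One section lets the single item carry the conclusion. Another has the PSM regression test the differences and brings the single item in as an addition. Nothing in the article reconciles the two, and the alpha sentence gives each test the full 0.05.

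Anticipated Results intends to derive direct recommendations on privacy enhancements from the aspect that is valued most. If the two instruments gave different answers, the article would support resting the claim on either one. No directional hypothesis limits that choice once the data are seen.

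A second difficulty is the scope of the ANOVA. It spans four versions, including the full-design version, whereas the question concerns three.

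**Working it through.** **The plan's own figure.** The relevant figure is alpha = 0.05 for each analysis (Proposed Analysis). The article states no error rate for objective 1 as a whole, so there is none to reproduce. The sample sizes of 256 and 350 do not enter the calculation.

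**Step 1. Roles, side by side.**

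| Section | PSM | Single overall item |
|---|---|---|
| Willingness-to-Pay Measure | named measure, descriptive | validates the PSM; also carries the comparisons and the conclusion |
| Proposed Analysis | ordinal regression tests the differences | ANOVA across four versions, in addition |
| Anticipated Results | used for the three aspects | used for the three aspects |

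The first two rows cannot both describe the deciding analysis.

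**Step 2. Error rate if a positive result on either test were enough.** This rule is an assumption; the article does not state it. Suppose each test is valid at 0.05 and the aspects do not differ.

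- Independent tests: 1 − (1 − 0.05)² = 1 − 0.9025 = 0.0975.
- Perfectly correlated tests: 0.05.

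Both instruments are answered by the same people about the same versions, so some correlation is expected, but the article gives no value. To fill in the range, each test was modelled as a 2-df omnibus comparison of three aspects. The score vectors were a ~ N(0, I₂) and b = r·a + √(1 − r²)·e, with e an independent N(0, I₂). Each sum of squares was compared with the 95% point of chi-square on 2 df, using 1,000,000 draws per value of r.

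| Assumed correlation r | P(at least one significant) |
|---|---|
| 0.3 | 0.0949 |
| 0.5 | 0.0915 |
| 0.7 | 0.0841 |
| 0.8 | 0.0787 |
| 0.9 | 0.0711 |
| 1 | 0.05 |

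The model treats both tests as comparisons of three aspects. It does not describe the four-version omnibus ANOVA as written.

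**Step 3. What the four-version omnibus tests.** Let the three single-aspect versions have the same mean m and the full-design version have mean m + d. The grand mean is m + d/4. The sum of squared deviations of the version means is 3(d/4)² + (3d/4)² = 3d²/16 + 9d²/16 = 0.75d². This is above zero whenever d is not zero. The omnibus null hypothesis is then false although the three aspects are valued identically. Only the contrasts among the three single-aspect versions, or a three-version test, address objective 1.

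**Step 4. After the fix.** With one deciding test at 0.05, the error rate for the three-aspect omnibus claim is 0.05. If both tests were kept as decisive with alpha split equally, independence would give 1 − (1 − 0.025)² = 0.0494.

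**The case against.** The strongest reply has four parts.

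- **The article does assign the conclusion.** A reader might infer that neither test is named as deciding. That goes too far: the Willingness-to-Pay Measure section ties the conclusion on the most valued aspect to the single item. This stands. What remains is that Proposed Analysis cuts across the assignment.
- **No either-suffices rule is written.** A reader might infer that the study runs at a false-claim rate of about 9%. The article does not say so. Its 0.05 is a per-analysis level, and the validating role of the single item suggests that agreement between instruments is sought. This stands too, so the figures in step 2 are conditional. A validating role still does not say what follows if the instruments disagree.
- **The aim is exploratory, and a fuller plan may settle the matter.** The article frames objective 1 as exploration without directional hypotheses, and its limitations concede that the measure does not give a reliable economic value. A fuller plan, not shown here, could name the deciding test. This lowers the weight of the point. It does not remove the conflict between two sections that are shown, nor the alpha sentence that covers both tests.
- **Making the single item decisive takes a side.** The PSM is the named measure, the sample size rests on its price model, and its regression is listed first. That is fair. However, the Willingness-to-Pay Measure section is the only place that links a measure to the conclusion on the most valued aspect, and it calls the PSM descriptive.

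It would also be tempting to quote how often the two tests would disagree. Such percentages depend on effect sizes that the article does not give, and naming a deciding test would not change them, so they do not measure this defect.

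**Conclusion.** The point holds in a limited form. The Willingness-to-Pay Measure and Proposed Analysis sections conflict on which test decides a main aim, and the alpha sentence gives each test the full 0.05. If a claim were allowed on either test, its false-positive chance would lie between 5% and 9.75%. That range rests on the either-suffices reading, on each test being valid at 0.05, and on an unknown between-instrument correlation.

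The four-version omnibus is a separate mismatch that needs no such assumption: it can reject with no difference among the three aspects.

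Neither analysis is shown to be invalid. The documents do not support saying that no deciding measure is named, or that the inflated rate is the plan's stated rule. The point is worth acting on because the repair is cheap and a practical recommendation depends on the answer.

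**What to change.** In Proposed Analysis:

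1. State that the deciding test for objective 1 is the within-subject test of the single overall item across the three single-aspect versions, with its post hoc contrasts, at two-sided 0.05. Any comparison with the full-design version is kept separate from this test.
2. State that the PSM price ranges and ordinal regressions are supportive and are reported as estimates with intervals. If they disagree with the deciding test, the disagreement is reported as such.
3. Amend the alpha sentence so that 0.05 for objective 1 attaches to the deciding test and not to every analysis of the same question.

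This follows the assignment already made in the Willingness-to-Pay Measure section. It changes wording only and needs no further participants or data. The downside is that a difference seen only in the PSM regression could not be claimed as confirmed.

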## Stepwise Procedures

The present experiment will be administered online using the web-based survey tool Qualtrics that allows designing, running, and collecting data through online experiments and surveys. The stepwise procedures of the experiment are as follows: After informed consent is given, participants will first answer a baseline measure that assesses if participants would be willing to pay for the current, free-of-charge version of Facebook. Afterward, participants will be presented a short vignette describing a scenario in which Facebook may consider developing premium versions of their service that would offer enhanced privacy for users in return for a monthly fee. In the first part of the online experiment, four hypothetical, privacy-enhanced premium versions of Facebook are presented consecutively and participants indicate their willingness-to-pay for each of the premium versions using the four questions of the PSM and the additional overall willingness-to-pay item (see Section Willingness-to-Pay Measure). Each privacy-enhanced version of Facebook is contrasted with the conventional, free-of-charge version of Facebook to facilitate comparability and increase participants’ understanding of the enhancements of the premium versions. To control for order effects, the three privacy-enhanced premium versions of Facebook (i.e., data collection, data control, and third party sharing) will be presented in randomized order. The fourth full-design premium version, which combines all three privacy enhancements in one version, will be presented last.

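### The ordinal logistic regressions that compare privacy versions are specified without a participant-level term, so if fitted as named their tests and intervals would not hold the 5% level

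*Protocol article*

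**What the plan says.** Stepwise Procedures sets up a fully within-person design: "four hypothetical, privacy-enhanced premium versions of Facebook are presented consecutively and participants indicate their willingness-to-pay for each of the premium versions". Willingness-to-Pay Measure specifies four price questions per version plus one overall item.

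Proposed Analysis then builds the price model: "five price ranges will be considered that are defined as discrete states with a continuous price variable and modeled as ordinal logistic regressions". It uses that model for inference: "Ordinal logistic regression models will be applied to test for statistical differences between" what participants would pay for each privacy aspect. It adds that "the regression models can be extended to multiple predictors", giving privacy concerns and socio-demographic characteristics as examples. A significance level of 0.05 applies to every analysis.

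Two other statements matter. The same Proposed Analysis paragraph specifies a repeated-measures ANOVA on the overall item. Anticipated Results says that the ordinal regressions together with the ANOVAs "will be employed to investigate within-subject valuations of the three privacy aspects".

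**The concern.** An ordinal logistic regression in its ordinary form treats each row as a separate piece of information. Here the rows come in blocks. One person's four prices for a version move together, and so do that person's prices across versions. The model as named contains nothing to represent this.

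The consequence differs by type of test:

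- **Version contrast.** Two errors pull in opposite directions. Ignoring the fact that each person serves as their own control makes the test too cautious. Counting several price rows per version as separate evidence makes it too liberal.
- **Person-level predictor.** The same value is repeated on all of a person's rows, so the test is too liberal.

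At stake are the price-model test of which aspect is valued more and any predictor added to the price model.

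**Working it through.** **Plan's own figure.** Participants gives a minimum of 256 for a precision of 0.05 and a value near 80%. Reading 80% as a proportion and taking z = 2 (my assumption), n = z²p(1−p)/e² = 4 × 0.16 / 0.0025 = 256. The number is reproduced. It is a precision figure and does not depend on the present point. I use it as the analysed sample size.

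**Row counts.** Four versions × 4 questions = 16 prices per person; the three single-aspect versions give 12. With four rows per version, 256 people yield 256 × 12 = 3,072 rows. With a grid of 15 prices they yield 256 × 3 × 15 = 11,520. The article does not say how many rows enter the model.

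**Direction, from the linear analogue.** Let σa², σb² and σe² be the between-person, person-by-version and residual variances of log price, with m rows per version and three versions. The ratio of true variance to the variance that independent rows imply is:

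- version contrast: (mσb² + σe²) / (σa² + σb² + σe²)
- person-level predictor: (3mσa² + mσb² + σe²) / (σa² + σb² + σe²)

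The first can fall on either side of 1. With m = 4 and SDs 0.8, 0, 0.3 it is 0.09 / 0.73 = 0.12 (too cautious). With SDs 0.3, 0.7, 0.3 it is 2.05 / 0.67 = 3.06 (too liberal). The second exceeds 1 whenever m > 1 and either σa or σb is above zero. These ratios indicate direction only, because the ordinal model is not linear.

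**Simulation.** Setup: 256 participants, three versions, no version effect and no predictor effect, nominal level 0.05. Each person's four log-price thresholds were drawn with the SDs shown (residual SD 0.3) and sorted. A proportional-odds model included log price, version and one person-level covariate. Wald tests used either independent-row standard errors or participant-clustered ones. In the four-row layout the question label is the ordered response; in the grid layout the response is the five-state price perception at each of 15 prices. There were 400 runs per four-row setting and 120 per grid setting. Entries are rejection rates.

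| Layout | SD person | SD person × version | Version, independent rows | Version, clustered | Predictor, independent rows | Predictor, clustered |
|---|---|---|---|---|---|---|
| 4 rows | 0.8 | 0 | 0.000 | 0.040 | 0.398 | 0.077 |
| 4 rows | 0.8 | 0.2 | 0.000 | 0.050 | 0.400 | 0.045 |
| 4 rows | 0.8 | 0.4 | 0.000 | 0.052 | 0.310 | 0.033 |
| 4 rows | 0.5 | 0.5 | 0.072 | 0.062 | 0.270 | 0.037 |
| 4 rows | 0.3 | 0.7 | 0.147 | 0.062 | 0.195 | 0.040 |
| 15 prices | 0.8 | 0 | 0.000 | 0.075 | 0.717 | 0.067 |
| 15 prices | 0.8 | 0.2 | 0.067 | 0.067 | 0.742 | 0.017 |
| 15 prices | 0.8 | 0.4 | 0.342 | 0.033 | 0.717 | 0.075 |
| 15 prices | 0.5 | 0.5 | 0.567 | 0.017 | 0.667 | 0.067 |
| 15 prices | 0.3 | 0.7 | 0.725 | 0.025 | 0.550 | 0.042 |

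The Monte Carlo standard error at a true 0.05 is √(0.05 × 0.95 / 400) = 0.011 for the four-row settings and √(0.05 × 0.95 / 120) = 0.020 for the grid settings. The clustered columns are therefore broadly compatible with 0.05.

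A separate set of runs with likelihood-ratio tests (120 to 200 per setting) showed the same pattern. At a cross-version correlation of 0.88 the version test rejected in 0–2% of runs with 5–10 price points, 15–17% with 20, and 49% with 50.

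**The case against.** **Nothing says the rows are independent.** A reader might infer that the plan commits to independent rows and that its p-values are invalid. The document does not support that. It names a model family and is silent on the correlation structure. Anticipated Results describes the ordinal analysis as within-subject, and Proposed Analysis speaks of intra-individual differences. Anticipated Results also drops the repeated-measures label from the ANOVAs, so a short name need not mean an independence assumption. In a condensed article the handling of dependence may sit in a fuller plan. This stands, and it makes the point conditional. It does not dispose of it: calling the question within-subject states a purpose, not a method, and the paragraph that sets out the tests supplies a repeated-measures form for one of them only.

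**The large figures come from assumed inputs.** Also true. The article gives no price grid and no variance components. With four rows per version, the layout closest to the four questions asked, the version test ranged only from 0.00 to 0.15.

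**The main conclusions have other routes.** Willingness-to-Pay Measure assigns the multiple comparisons among the three aspects to the overall item, which is analysed by repeated-measures ANOVA. The theoretical model is tested by structural equation modelling on willingness-to-pay for the full-design version, one value per person. Adding predictors to the ordinal model is optional. All this stands and limits the severity. However, the overall item is also meant to validate the price-model results, and it cannot correct inference made on the four-question data.

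**Conclusion.** The point holds in conditional form, at moderate severity. The ordinal regression is assigned formal tests on data in which each person supplies every version and several prices per version, and no device for that dependence is named. Fitted as named, it would not hold 5%. Under the assumed inputs the version contrast ranged from 0.00 to 0.73 and could be conservative or anti-conservative; person-level predictors were anti-conservative throughout, at 0.20 to 0.74. Participant clustering gave 0.02 to 0.08.

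The exact rates depend on row counts and variance components that the document does not give. That the error can go either way for versions, and only one way for predictors, follows from the design and does not depend on those choices. It would be wrong to conclude that the study's comparison of aspects or its psychological model is invalid, because the ANOVA and the structural equation model do not share this problem.

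**What to change.** Keep the ordinal logistic fit for the price curves and their maxima. Add one sentence to Proposed Analysis: the participant is the unit of analysis, and all tests and confidence intervals from the ordinal models, for versions and for predictors, use participant-clustered standard errors or a bootstrap that resamples whole participants with all their versions and price rows. Either option leaves the fitted curves unchanged. A participant random intercept alone would not be enough, because it does not absorb person-by-version variation when several price rows per version are stacked.

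The cost is a few lines of R and possibly wider intervals for the predictors. No new data are needed.

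### The PSM price range and fitted maxima are one sample-level value per version, so they cannot carry the intra- and inter-individual tests the plan assigns to them

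*Protocol article*

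**What the plan says.** All of the following stands in the Proposed Analysis section of the protocol article, in this order.

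- Step one sets the level of the curves: "a cumulative frequency will be calculated for each of the enhanced privacy aspects captured in the hypothetical premium versions of Facebook". The unit is the premium version.
- Step two introduces the acceptable range at a different level: "the range of acceptable prices that each participant is willing to pay for the different privacy-enhanced premium versions will be determined". Its endpoints are then defined on the curves. For the lower one, "Marginal cheapness is determined by the point where the cumulative frequencies of “too cheap” prices (reversed) and “cheap” prices intersect"; for the upper one, "the point of marginal expensiveness is determined by the intersection of the cumulative frequencies of “too expensive” prices (reversed) and “expensive” prices".
- Step three follows the ordinal logistic approach to five price-perception intervals: "the logistic cumulative probabilities for each price threshold will be determined and the appropriate thresholds for the particular model will be subtracted". The peak of the resulting curve is the outcome: "These maxima will be used as a proxy for participants’ willingness-to-pay".
- After naming ordinal logistic regression as the test for differences between versions, the section adds that, together with the range, "the proxies will be used to test for intra-individual and inter-individual differences between willingness-to-pay for the four privacy-enhanced premium versions".

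Two other sections bear on the point. Willingness-to-Pay Measure gives each participant four PSM price questions and one overall item per version, and assigns the comparison of the three privacy enhancements to the overall item. Anticipated Results describes the price range per privacy aspect, not per person.

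**The concern.** A test of intra-individual differences needs, for each person, a value under at least two versions. A test of inter-individual differences needs a value for each person that can vary across people. The plan names the range and the fitted maxima as the values to use, but defines both on curves that pool all respondents.

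An analyst following the text would have to compare four numbers by eye or invent a participant-level quantity after the data are in. The first gives no error estimate. The second leaves open a choice that should be fixed beforehand, since α = 0.05 is to apply to all analyses. Any statement about individual differences in PSM-derived prices would rest on one or the other.

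**Working it through.** The plan states no figure here, so there is none to reproduce. The check is how many values the definitions return, and for what unit.

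**Inputs.** Four premium versions (Experimental Design); four PSM prices per person per version (Willingness-to-Pay Measure); at least 350 participants (Participants); the definitions quoted above.

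**Step 1: write out the definitions.** For one version, let F_tc, F_c, F_e and F_te be the shares of the sample whose too-cheap, cheap, expensive and too-expensive answers lie at or below price p.

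- Lower endpoint (MGP): 1 − F_tc(p) = F_c(p), that is F_tc(p) + F_c(p) = 1.
- Upper endpoint (MEP): 1 − F_te(p) = F_e(p), that is F_e(p) + F_te(p) = 1.
- Willingness-to-pay proxy: the p that maximises the fitted F_c(p) − F_e(p).

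Every term is a function of the sample distributions. No term carries a participant index.

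**Step 2: count the output at the planned size.** I simulated prices for n = 350 in each of four versions. The price distributions are assumed, as is the form of the fit (logistic in log price, common slope). They serve only to show what the procedure returns.

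| Version | MGP | MEP | Maximum |
|---|---|---|---|
| 1 | 2.01 | 4.05 | 2.88 |
| 2 | 2.28 | 4.63 | 3.37 |
| 3 | 2.76 | 5.54 | 3.92 |
| 4 | 2.92 | 5.80 | 4.12 |

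That is 4 ranges and 4 maxima. A participant-level measure would give 350 × 4 = 1,400 values and 350 within-person differences for each pair of versions.

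**Step 3: try the definitions on one person.** Take illustrative answers 1, 2, 4 and 6.

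- F_tc is 1 from price 1 and F_c is 1 from price 2, so F_tc + F_c = 1 for every price from 1 up to 2. There is no single MGP.
- F_e is 1 from price 4 and F_te is 1 from price 6, so F_e + F_te = 1 for every price from 4 up to 6. There is no single MEP.
- F_c − F_e equals 1 for every price from 2 up to 4. The logistic fit separates perfectly (coefficients about −517, 686 and −449), so its slope and peak are not identified.

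The definitions therefore do not yield a personal range or maximum even when applied person by person.

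**Step 4: what the summaries can support.** Resampling the 350 simulated participants 200 times gave a standard error of about 0.10 for one maximum. Sampling error for the maxima can thus be obtained at sample level. Only the individual-level use fails.

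**The case against.** The strongest reply is that little depends on this sentence. The Willingness-to-Pay Measure section gives the question of which aspect is valued most to the single overall item. Proposed Analysis examines that item by repeated-measures ANOVA with post hoc tests. That is participant-level data with a proper within-person error term. The sentence just before the disputed one plans ordinal logistic regression for differences between versions and allows predictors such as privacy concerns. Those models are fitted to participants' answers, and how they handle repeated answers may be left to a fuller analysis plan. The PSM is itself called descriptive.

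Most of this stands, and it limits the point. It does not rescue the disputed sentence, which gives the intra- and inter-individual tests to the proxies and the range, in addition to the ordinal models and the ANOVA. Adding covariates to the ordinal models would give a maximum for each covariate profile, still not for each person.

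Two stronger readings are tempting. A reader might infer that the study has no valid way to say which privacy aspect is valued most. The ANOVA on the single item contradicts that. A reader might also infer that the plan claims a fitted maximum for each participant. The explicit statement concerns the range only. For the maxima, the plural reference to participants can be collective, and the individual level enters only through the test assigned to them.

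**Conclusion.** The point holds in a limited form. The phrase tying the range to each participant contradicts the plan's own definitions, and the intra- and inter-individual tests assigned to the range and maxima have no participant-level data to work on: four values of each summary, one per version. This follows from the definitions and does not depend on the simulated prices.

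The defect is confined to tests based on the PSM range and maxima. The ANOVA on the single item is unaffected, the ordinal models could compare versions, and differences between the maxima can be assessed at sample level by bootstrap. It should be corrected before analysis because a stated inferential analysis cannot be carried out as written, but it does not undermine the comparison of the three privacy aspects.

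**What to change.** 1. **Range and maxima.** In Proposed Analysis, replace the per-participant wording with one sample-level range per premium version, and label the maxima the same way. Report each range, each maximum and each between-version difference with a 95% interval from a bootstrap that resamples whole participants, keeping each person's answers to all four versions together so that their correlation carries into the differences.

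2. **Individual-level tests.** Base them on participant-level data, either the single overall item or the raw PSM answers, in a model with version as a fixed effect and participant as a random effect. Say in advance which measure is used. Person-level predictors can enter the same model for the inter-individual questions.

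3. **Presentation position.** Estimate it only among the three versions shown in randomised order. Stepwise Procedures always places the full version last, so with categorical terms the indicator for the full version and the indicator for the fourth position are the same column, and the two effects cannot be separated. Contrasts of the full version with the others should be reported with that limitation.

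The cost is a few changed sentences and a little extra analysis work. All the data needed are already to be collected.
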